### Data collection, management, and analysis

2.9

The data is collected continuously using the Res@t app with the ISO-certified Embloom platform as the backend. Furthermore, the PsychoEQ programme, which facilitates the collection of questionnaire data via mobile phones, tablets and personal computers, is employed. All data pertaining to participants will be pseudonymized.

Descriptive statistics are presented separately for each group and for the total sample. The data will be analysed using IBM SPSS 28 Statistics. A complete-case analysis will be conducted on the main outcome variable, the specific DMUD score, which will be evaluated at five points in time: baseline, interim, post-intervention, follow-up 1, and follow-up 2 (see **Table 1** and **Figure 2**). In order to determine whether there are notable differences in the impact of the treatment, a mixed ANOVA will be used, with the specific DMUD scores serving as the dependent variable and time and group serving as the within-subject factors and between-subject factors, respectively.

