**Methods:**

The efficacy of Res@t digital, initially conceived as an adjunct to child and adolescent psychiatric treatment, is to be evaluated for n= 32 children and adolescents with a media use disorder or at risk of developing this disorder, and their families enrolled in child and youth welfare services. The efficacy of the app will be evaluated in a randomised controlled trial with a waitlist control group. The primary outcome is the reduction of DMUD symptoms over a 20-week period following the onset of app training. Secondary outcomes include EEG measurements and changes in standardised psychopathological variables.

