### Sample size

2.6

Calculating the sample size for the primary outcome of the change in the severity of DMUD or hazardous use pattern between the intervention and control group over 5 measurement points is based on a mixed ANOVA with repeated measures and a within-between interaction. Assuming an effect size of 0.20, alpha error probability.05 and power.8, GPower 3.1.9.7 calculated a total sample size of 32 subjects with 16 per group. Due to the high-risk conditions of the target group, we assume a drop-out rate of 50%, which results in a total of 64 subjects to be recruited.

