**Figure 2 f2:**
[figure not shown]
Study flowchart of participants. DMUD, digital media use disorder; EEG, Electroencephalography; TAU, treatment as usual.

**Table 1 T1:** Measurement time points.

[figure not shown]

Time points: t_0_ = Screening (< week 0), t_1_ = Baseline (week 0), t_2_ = Interim (week 5), t_3_ = Post-intervention (week 10), t_4_ = Follow-up 1 (week 15), t_5_ = Follow-up 2 (week 20). GADIS-A, Gaming Disorder Scale for Adolescents; SOMEDIS-A, Social Media Disorder Scale for Adolescents; STREDIS-A, Streaming Disorder Scale for Adolescents; SDQ, Strength and Difficulties Questionnaire; PSQI, Pittsburgh Sleep Quality Index; ISI, Insomnia Severity Index; ESS-CHAD, Epworth Sleepiness Scale - Children and Adolescents; PSS-10, Perceived Stress Scale; Family APRGAR, Family Functionality; FCS, Family Communcation Scale; MAAS-5, Mindfulness Attention Awareness Scale; FEVER, Questionnaire for the Assessment of Readiness to Change; EEG, Electroencephalography; GADIS-P, Gaming Disorder Scale for Parents; SOMEDIS-P, Social Media Disorder Scale for Parents; STREDIS-P, Streaming Disorder Scale for Parents; SDQ-f, Strength and Difficulties Questionnaire – External Assessment; PHQ-9, Patient Health Questionnaire; GAD-7, Generalized Anxiety Disorder Questionnaire; EEI-R, Parenting Inventory - Revised; FSW, Parental Self-Efficacy; ULQIE, Ulm Quality of Life Inventory for Parents of Chronically Ill Children.

In the event of missing values, a sensitivity analysis will be conducted in accordance with intention-to-treat principles. Missing values will be assumed to be missing at random and handled using the multiple imputation method. A baseline-adjusted linear mixed model will be calculated with random intercept for patient, group and timepoint as well as their interaction as main effects and respective baseline value as covariate. The threshold for statistical significance of the primary outcome is set at p < 0.05. Further outcomes are analysed in an exploratory manner.

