## Discussion

3

The Res@t digital intervention aims to close a gap in the treatment and care of adolescents with DMUD and their parents. The aim of this study is to test the effectiveness and efficacy of an evidence-based training programme for high-risk groups such as adolescents in child and youth services. In this kind of setting, the DMUD or hazardous use pattern is embedded in highly stressed adolescents and family members, whereby awareness of the problem and motivation for treatment as well as family support regarding the DMUD are likely to differ from adolescents who are undergoing primarily treatment. It is possible that the highly individual circumstances and conditions in which children and young people supported by youth and social services live may limit the generalisability of the findings on the usability and efficacy of Res@t digital. The same applies to the subsample concerning school-related difficulties. Nevertheless, the efficacy of Res@t digital will be further examined in the main study (32) of outpatients diagnosed with DMUD, recruited from psychotherapeutic and psychiatric practices and hospitals. To address the presumably harder-to-reach high-risk target group, we use a high dose of reinforcement in the form of gift cards every five weeks. It is hypothesised that this reinforcement system will be effective when used in conjunction with a blended approach, in which personal contact is intended to ensure the successful implementation of the intervention. Study staff will then support adolescents and parents with motivational barriers, technical issues, or organising app implementation. Combining digital and face-to-face components to address the various challenges of participation may be innovative, but not universally effective. For example, adolescents with high levels of stress or low motivation may benefit less from the digital component, or face-to-face contact may be a barrier for those who are socially averse. Furthermore, the lack of blinding in a waitlist design could lead to participants in the IG being influenced by expectations of their group allocation, leading to placebo effects and biased results. Participants in the CG could feel disadvantaged, which could change their perception and response to the use of digital media. In addition, the lack of intervention could lead to reduced adherence if participants feel inappropriately treated. Another limitation is the acquisition of neurophysiological parameters using EEG in the participants’ homes rather than under laboratory conditions. This results in a higher validity of the media use measures, but may lead to an overall lower reliability caused by environmental factors. Despite the limitations mentioned, a positively evaluated Res@t app can represent a low-threshold treatment option compared to outpatient and inpatient treatment and serve as a motivational tool to facilitate entry into further treatment in a therapeutic setting. The evaluation will also show whether the combination of Res@t digital with the blended approach and reinforcement strategies has the potential to be an effective treatment option for hard-to-reach adolescents at high-risk, underscoring the need for real people to accompany the digital.

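### The primary test is a complete-case mixed ANOVA although 50% drop-out is planned, which leaves the confirmatory result open to bias in either direction

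*Protocol article*

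**What the plan says.** Section 2.9 fixes the analysis set for the primary outcome: "A complete-case analysis will be conducted on the main outcome variable, the specific DMUD score", at five time points. The method follows: "a mixed ANOVA will be used, with the specific DMUD scores serving as the dependent variable", with time as the within-subject and group as the between-subject factor.

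Section 2.6 plans for heavy attrition. The software "calculated a total sample size of 32 subjects with 16 per group", and then "we assume a drop-out rate of 50%, which results in a total of 64 subjects to be recruited". The Abstract presents only the smaller number: the app "is to be evaluated for n= 32 children and adolescents".

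After Table 1, section 2.9 adds: "In the event of missing values, a sensitivity analysis will be conducted in accordance with intention-to-treat principles". That analysis uses multiple imputation under missing at random and a baseline-adjusted linear mixed model with a random intercept. The p < 0.05 threshold is attached to the primary outcome.

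Section 2.8 states that nobody is blinded. The Discussion concedes that in the control group "the lack of intervention could lead to reduced adherence if participants feel inappropriately treated".

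**The concern.** A repeated-measures ANOVA on complete cases uses only participants with all five scores. The plan expects half of those recruited to be lost, so the confirmatory test compares the people who stayed. If staying is linked to outcome differently in the two arms, the arms compared are no longer the arms that randomisation formed. The protocol gives reason to take this seriously: allocation is known to all, one arm waits, and the authors themselves expect that waiting may reduce adherence.

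Two features add to the problem. The analysis that keeps all randomised participants is already foreseen but ranks second, and is conditional on missing values that the plan treats as near certain. Listwise deletion also removes anyone who misses one visit, together with the scores that person did give.

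At stake is the one confirmatory p-value of the trial.

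**Working it through.** **1. The plan's own figures.** From 2.6: effect size 0.20 (read as Cohen's f), alpha 0.05, power 0.80, two groups (k = 2), five measurements (m = 5), within-between interaction. Not stated, so assumed: correlation rho = 0.5, sphericity (epsilon = 1).

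- Noncentrality = f² × N × m / (1 − rho) = 0.04 × 32 × 5 / 0.5 = 12.8.
- df1 = (k − 1)(m − 1) = 4; df2 = (N − k)(m − 1) = 30 × 4 = 120.
- Power at N = 32 is 0.814; at N = 30 it is 0.783. The smallest even N is 32, as stated.
- 32 / (1 − 0.5) = 64, as stated.

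The required N depends on the unstated correlation: 44 at rho = 0.3, 38 at 0.4, 26 at 0.6.

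**2. Who is left out.** On the plan's figures, 64 − 32 = 32 of those recruited are outside the primary test. Listwise deletion could cause such a loss without anyone leaving the study: with 16% independent missingness at each of the four later visits, 64 × 0.84⁴ = 31.9 complete cases remain.

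**3. What selection does when the app has no effect.** The check simulated 64 randomised 1:1, five visits, correlation 0.5 between visits, no treatment effect and about 50% drop-out. The probability of leaving followed a logistic function of change from the first score. The mechanisms are assumptions; the document gives none. Bias is the app-minus-waitlist difference in change, in SD; negative favours the app. The all-data analysis is a likelihood-type model on every observed score.

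| Assumed mechanism | Complete-case type I error | Complete-case bias | All-data type I error | All-data bias |
|---|---|---|---|---|
| Unrelated to outcome | 5.7% | about 0 | 4.9% | about 0 |
| Non-improvers leave both arms equally (log-odds 1; 2 per SD) | 5.2%; 5.1% | about 0 | – | – |
| Non-improvers leave app arm only, observed interim change, log-odds 1 | 12.2% | −0.26 | 4.7% | −0.01 |
| Same, log-odds 2 | 21% | −0.38 | 4–5% | within about 0.02 |
| Non-improvers leave waitlist arm only, log-odds 1 to 2 | 13–27% | +0.25 to +0.41 | – | – |
| App arm only, leaving depends on unobserved later scores, log-odds 1 | 10.0% | −0.28 | 6.9% | −0.11 |

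The rows come from runs of 800 to 3,000 data sets. With 2,000 runs the Monte Carlo standard error at 5% is √(0.05 × 0.95 / 2000) = 0.5 percentage points. Repeat runs with slightly different drop-out set-ups put the one-arm case at about 13 to 28%. The log-odds 1 all-data results used the true covariance, so a fitted model may do slightly less well at this sample size.

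**4. Reading the table.** Error is inflated only where the mechanism differs by arm, and the sign follows the arm that loses its non-improvers. The all-data model removes the bias when leaving depends on observed scores and reduces it when leaving depends on unobserved ones.

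**The case against.** The best defence is that the plan is coherent on its own terms. It was sized for completers, it pre-specifies an intention-to-treat analysis that would expose a discrepancy, and it acts against attrition with visit-by-visit vouchers (2.7) and face-to-face support (2.1, Discussion). This stands as mitigation. But the article does not say which result prevails if the two analyses disagree, and the complete-case result is the one ranked first.

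A reader might draw stronger conclusions that the document does not support:

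- *That half of the randomised adolescents are discarded.* Section 2.6 says 64 are to be recruited. It does not define drop-out or split it into losses before and after randomisation, so the share of randomised participants lost may be smaller. Nor does it say whether missed visits come on top of the 50%.
- *That randomisation is certain to fail.* If leaving is unrelated to outcome, or equally related in both arms, the test keeps its level.
- *That the plan would show benefit from an ineffective app.* The sentence in the Discussion on adherence concerns the control arm and does not tie leaving to outcome. If waitlisted non-improvers leave, the bias runs against the app. Opposite selection in the two arms gives 41 to 50% error, but nothing in the text suggests it.
- *That the primary test is underpowered.* Power of about 0.41 with 32 completers arises for a 0.65 SD difference at all four later visits. That corresponds to f = √(0.65² × 0.25 × 0.16) = 0.13, not the planned 0.20. At 0.20 the power is 0.81.
- *That a missing-not-at-random analysis has been omitted.* Such an analysis is commonly left to the statistical analysis plan, which is not shown.

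**Conclusion.** The concern holds as a risk of bias of unknown direction. The ranking of the analyses is stated in the article, so it is not a detail left to another document.

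Under no true effect, rho = 0.5 and about 50% drop-out, the complete-case type I error is about 5% with harmless or equal drop-out. It is about 13 to 28%, with a bias of roughly 0.3 to 0.4 SD either way, if leaving depends on non-improvement in one arm only. These sizes rest on assumed mechanisms and would shrink if part of the 50% is lost before randomisation. The conclusion that the all-data model is less exposed rests on missing at random. Where leaving depends on unobserved scores, some bias remains (about 0.11 SD in the case run). The planned numbers of 32 and 64 are not in error.

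**What to change.** In section 2.9, reverse the order of the two analyses. Make the intention-to-treat linear mixed model, on all randomised adolescents as allocated and with their available DMUD scores, the single primary analysis at p < 0.05. Keep the complete-case mixed ANOVA as supportive. Delete the condition that makes the intention-to-treat analysis depend on missing values occurring. The model now described uses the baseline value as covariate together with multiple imputation, so the new text should state how baseline enters and whether imputation is kept.

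In the Abstract, give 64 to be recruited and 32 expected completers. In 2.6, say how much of the 50% is expected before and how much after randomisation.

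The cost is wording and some analysis work: no extra participants or visits, and a model of this type is already planned. The downside is reliance on missing at random, which is a weaker assumption than complete-case analysis generally needs. A sensitivity analysis that departs from missing at random is optional and may sit in the statistical analysis plan.

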Our trial aims to test the hypothesis of the superiority of Res@t digital combined with child and youth welfare service through a greater reduction in the symptoms of the most prominent DMUD or hazardous use pattern in the individual adolescent, compared to child and youth welfare service alone. Primary hypothesis: Res@t+TAU reduces symptoms of specific DMUD in adolescents compared with TAU alone, measured as a group-by-time interaction over 5 measurement points from screening to a 10-week follow-up. Secondary hypotheses: a) Res@t+TAU reduces symptoms of specific DMUD in adolescents as assessed by their parents compared with TAU alone, measured as a group-by-time interaction over 5 measurement points from screening to a 10-week follow-up. b) Res@t+TAU reduces symptoms of specific DMUD in adolescents assessed by authorised personnel compared with TAU alone, measured as change from screening to post-intervention. c) Res@t+TAU will have a beneficial influence on several observation-based constructs related to DMUD in adolescents (improved readiness to change and sleep quality), in parents (improved life satisfaction and family self-efficacy) and in both adolescents and parents (reduced stress levels and improved family functioning and mindfulness) compared with TAU alone, measured as change from baseline to post-intervention. d) Res@t+TAU reduces DMUD typical or potential markers in the EEG compared with TAU alone, measured as change from baseline to post-intervention.

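### The primary mixed ANOVA uses the pre-treatment DMUD score as an outcome level and not as a covariate; it reaches its stated 80% power but gives up precision that a baseline-adjusted joint test would recover

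*Protocol article*

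**What the plan says.** Three places in the protocol article fix the same confirmatory test.

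- **Section 1.2** states the primary hypothesis as an effect "measured as a group-by-time interaction over 5 measurement points from screening to a 10-week follow-up".
- **Section 2.6** sizes the trial "based on a mixed ANOVA with repeated measures and a within-between interaction". The inputs are given as "Assuming an effect size of 0.20, alpha error probability.05 and power.8", and the software "calculated a total sample size of 32 subjects with 16 per group".
- **Section 2.9** states that "A complete-case analysis will be conducted on the main outcome variable", namely the specific DMUD score, "evaluated at five points in time: baseline, interim, post-intervention, follow-up 1, and follow-up 2", and that "a mixed ANOVA will be used, with the specific DMUD scores serving as the dependent variable". Time and group are the factors. No covariate is named.

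Sections 1.2 and 2.5.1 call the first of the five points screening and section 2.9 calls it baseline. It precedes treatment under either label, and this point does not turn on which is meant.

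The last paragraph of section 2.9, after Table 1, describes a second model: a linear mixed model with a random intercept, group, time point, their interaction, and the "respective baseline value as covariate". It belongs to a sensitivity analysis that is triggered by missing values.

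**The concern.** When the pre-treatment score is one of the outcome levels, the 4-df group-by-time interaction is a test of the four changes from that score. The pre-treatment score is subtracted with a slope of exactly 1, so its full measurement noise enters every contrast. Under 1:1 randomisation both arms have the same expected pre-treatment mean. Estimating the slope instead of fixing it at 1 then removes noise and introduces no bias.

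With 16 analysed adolescents per arm, chance imbalance in this score is likely. The plan already accepts the adjustment for its sensitivity model, but withholds it from the only analysis with a stated significance threshold. At stake is the precision of the confirmatory result in a small trial that expects 50% drop-out and analyses complete cases.

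**Working it through.** **Inputs from the document.** N = 32 (16 per arm), f = 0.20, alpha 0.05, power 0.80, two groups, five time points (section 2.6).

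**Assumptions.** The article gives no correlation between visits (rho) and no sphericity value. I take equal variances (set to 1), equal correlations and rho = 0.5, and vary rho from 0.3 to 0.7. The value 0.5 reproduces N but is not identified by it: rho 0.6 with epsilon 0.75, or rho 0.7 with epsilon 0.5, also returns 32.

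**Step 1: reproduce the plan's N.** For the within-between interaction, lambda = f² × N × m / (1 − rho) = 0.04 × 32 × 5 / 0.5 = 12.8, with (2 − 1)(5 − 1) = 4 and (32 − 2)(5 − 1) = 120 df. Power is 0.814. At N = 30 it is 0.783. So 32 is reproduced.

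**Step 2: compare the noise.** The covariance of the four changes is (1 − rho)(I + J). The covariance of the four post-treatment scores given the pre-treatment score is (1 − rho)I + (rho − rho²)J. For the mean of the four visits at rho = 0.5:

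- changes: 0.5 × (1/4 + 1) = 0.625
- adjusted scores: 0.5/4 + 0.25 = 0.375, which is 40% lower.

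**Step 3: compare the power.** Each effect shape is scaled to f = 0.20. An effect that is constant from week 5 is then 1.0 SD at each of the four visits. The noncentrality is (16/2) × d′V⁻¹d. For the constant effect this is 8 × 4/2.5 = 12.8 on changes, which agrees with step 1, and 8 × 4/1.5 = 21.3 on adjusted scores. Power of the adjusted joint test (group plus group-by-time, 4 df) uses 4 and 112 df and a small-sample factor of 1 − 1/29.

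| Effect shape (rho = 0.5) | Planned ANOVA | Noncentrality, adjusted | Adjusted joint test | Same, simulated | Adjusted 1-df average | Adjusted interaction alone |
|---|---|---|---|---|---|---|
| Constant from week 5 | 0.81 | 21.3 | 0.96 | 0.96 | 0.99 | 0.05 |
| Ramp, then plateau | 0.81 | 19.3 | 0.94 | 0.94 | 0.97 | 0.26 |
| Peak at week 10, then fading | 0.81 | 18.7 | 0.93 | 0.93 | 0.95 | 0.34 |
| Linear build-up | 0.81 | 17.1 | 0.91 | 0.91 | 0.87 | 0.53 |
| From week 10 only | 0.81 | 16.0 | 0.89 | 0.89 | 0.77 | 0.63 |
| From week 15 only | 0.81 | 14.2 | 0.84 | 0.85 | 0.43 | 0.77 |

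The simulation used 12,000 runs per cell. All tests rejected a true null in 4.8% to 5.4% of runs.

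**Step 4: vary rho.** These are gains of the joint test over the ANOVA for effects present by week 10.

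- rho 0.3: ANOVA 0.65, joint test 0.82 to 0.96, a gain of 17 to 31 points (about 8 if onset is at week 15).
- rho 0.5: gain of 7 to 15 points (about 3 if onset is at week 15).
- rho 0.7: ANOVA already 0.97, gain of about 1 to 2 points.

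**Step 5: which adjusted test.** Once the pre-treatment score becomes a covariate, the interaction covers only the post-treatment visits and misses a constant effect altogether (power 0.05). The interaction alone is weaker than the planned ANOVA for every shape. The 1-df average is strongest for early effects but falls below the ANOVA for onset at week 10 or later. Only the joint test gains for every shape shown.

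**The case against.** The planned test is valid, and hypothesis, sample size and analysis agree on it. It reaches the power it was designed for. One can fairly call this a less efficient choice rather than a mistake, and that stands.

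The plan also contains a baseline-adjusted model. With 50% drop-out assumed in section 2.6, its missing-data trigger will very probably be met. This stands too: the adjusted analysis is likely to appear, but as a sensitivity analysis that cannot carry the confirmatory conclusion.

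The size of the gain rests on a correlation, equal variances and an effect shape that the article does not state. Section 2.2 also admits only adolescents who reach a cut-off on these same scales. Such selection narrows the pre-treatment variance and leaves the slope unchanged, so the added noise, (1 − slope)² × Var(pre), shrinks. A simulation with normal scores, rho 0.5 before selection, truncation at the 50th, 70th or 90th percentile, and the effect rescaled to ANOVA power of about 0.8 gave gains of roughly 5 to 11 points for constant, linear and peaked effects. For onset at week 15 it gave 0 to 2 points. The gain survives but is smaller.

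Finally, the remedy changes the tested effect, so it is more than a change to the model. That is correct, and section 1.2 has to change with section 2.9.

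**Conclusion.** The point holds as an efficiency loss in the primary analysis. The gain from adjustment is about 7 to 15 points of power at N = 32. This is conditional on rho near 0.5, equal variances and an effect present by week 10. Outside those conditions it runs from almost nothing (rho 0.7, or late onset) to about 31 points (rho 0.3).

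Three stronger readings are tempting and not supported.

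- A reader might infer that the trial is underpowered or the ANOVA biased. The stated 80% is met under the inputs that reproduce the plan's own N, and the type I error is held.
- A reader might take the lost power as a fixed property of the plan. The article states none of the quantities that determine it.
- A reader might think that promoting the existing sensitivity model is enough. If its interaction were then tested alone, power would fall.

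The change is worth making because the covariate is already collected and the cost is small.

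**What to change.** - **Section 2.9:** make the primary model a repeated-measures model of the four post-randomisation DMUD scores (weeks 5, 10, 15 and 20) with group, time, group-by-time and the pre-treatment score as covariate. Name which pre-treatment measurement is used.
- **Confirmatory test:** use the joint 4-df test of group plus group-by-time. Do not test the interaction alone, and do not rely on the 1-df average as the sole test.
- **Section 1.2:** reword the primary hypothesis as an adjusted group difference across the four post-randomisation visits.
- **Secondary hypothesis a:** apply the same model to the parent-rated score, as an exploratory analysis.
- **Supporting analysis:** keep the planned mixed ANOVA.

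N = 32 can stay. The change should be made before analysis and needs no new data or participants. The costs are one degree of freedom for the covariate, a reworded primary hypothesis, and a sample-size formula in section 2.6 that no longer matches the primary test exactly.
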